# Clinical efficacy study on the efficacy and safety of acupuncture for post-stroke dysphagia based on the regulation of the swallowing neural circuit: protocol for a multicenter, open-label, randomized controlled trial

**DOI:** 10.3389/fmed.2025.1697235

**Published:** 2025-12-10

**Keywords:** dysphagia, stroke, acupuncture, fMRI, sEMG, study protocol

## Abstract

**Introduction:**

Post-stroke dysphagia (PSD) is a common complication of stroke. Rehabilitation training and acupuncture have been suggested as current effective therapies, but high-quality evidence of acupuncture is insufficient. A meta-analysis has shown that acupuncture may be an effective adjunctive treatment for improving swallowing function, but the guidelines do not provide sufficient recommendations. Therefore, clinical and mechanism-related research on acupuncture treatment for post-stroke dysphagia should be vigorously promoted.

**Methods:**

This study is a multicenter, open-label, randomized clinical trial. A total of 115 participants will be enrolled: 100 PSD patients will be randomly allocated in a 1:1 ratio to the experimental group (acupuncture combined with basic treatment) or the control group (rehabilitation training combined with basic treatment), and 15 healthy controls will only provide baseline information without receiving any treatment. Both groups will be given a 4-week intervention (three times per week). The primary efficacy outcome measure is the Functional Oral Intake Scale (FOIS). Secondary outcome measures include: Regional Homogeneity (ReHo) and Amplitude of Low-Frequency Fluctuation (ALFF) metrics from Functional Magnetic Resonance Imaging (fMRI) scans, surface electromyography (sEMG) assessments, the Swallowing Disorders-Specific Quality of Life Questionnaire (SWAL-QOL), the National Institutes of Health Stroke Scale (NIHSS), the Treatment Expectation Questionnaire (TEX-Q) and patient-reported outcomes (PRO). Additionally, the Fiberoptic Endoscopic Evaluation of Swallowing (FEES) will be performed together with the Penetration-Aspiration Scale (PAS) and the Yale Pharyngeal Residue Severity Rating Scale (YPR-SRS). Outcomes will be assessed at five time points: Baseline, day 15 and day 30 during treatment, and 30 and 60 days after treatment. All primary analyses will be conducted using both intention-to-treat and per-protocol approaches.

**Discussion:**

This trial will investigate the efficacy of acupuncture targeting swallowing neural circuit regulation for improving swallowing function, reducing major complications, and enhancing quality of life in patients with swallowing disorders. It will also explore the underlying neural regulatory mechanisms, evaluate the efficacy of acupuncture for post-stroke dysphagia, and provide high-quality evidence.

**Clinical trial registration:**

https://itmctr.ccebtcm.org.cn/mgt/project/user/project-view/F5B9D5CA-0B85-47BD-8911-5B2B0DDD4EB5, identifier ITMCT R2025001435.

## Introduction

1

In 2020, the incidence of stroke among adults in China was reported as 310.0 cases per 100,000 person-years (1), and epidemiological projections suggest a sustained increase from 2019 to 2050 (2). Currently, the incidence of post-stroke dysphagia ranges from 37 to 78% (3). Dysphagia can lead to dehydration, malnutrition, aspiration pneumonia, and other complications (4), and may also exacerbate post-stroke mortality and disability (5).

The main treatments for post-stroke dysphagia (PSD) include behavioral interventions, rehabilitative training, pharmacotherapy, and neuromuscular electrical stimulation (NMES) (6). The 2021 AHA/ASA Guidelines for Adult Stroke Rehabilitation (originally published in 2016) suggest that acupuncture may be considered as an adjunctive therapy for dysphagia (Class IIb recommendation, Level B evidence). Clinical studies (7–9) increasingly support the therapeutic benefits of acupuncture in improving swallowing function after stroke (10). Neurophysiological research (11) has clarified the modulatory pathways of the swallowing neural circuit, indicating that acupuncture may act through targeted modulation of this network. These findings provide a mechanistic basis for further research on acupuncture in pathological conditions.

This study aims to evaluate acupuncture’s therapeutic efficacy for post-stroke dysphagia (PSD) by rigorously comparing it with conventional swallowing rehabilitation. Although previous research has demonstrated acupuncture’s potential benefits, direct comparisons with established rehabilitation methods remain lacking. Moreover, the neural mechanisms underlying acupuncture’s effects on PSD require further clarification. Given the substantial differences between acupuncture and rehabilitation procedures in clinical trials, implementing a single-blind design is challenging. Therefore, an open-label, multi-center, randomized controlled trial will be adopted to comprehensively evaluate the efficacy of acupuncture for PSD patients, clarify the neural mechanisms involved in acupuncture intervention for post-stroke dysphagia and obtain high-quality evidence-based data.

## Methods and analysis

2

### Objective

2.1

This study aims to explore acupuncture’s efficacy in post-stroke dysphagia (PSD) patients, clarify the neural mechanisms of acupuncture intervention for PSD, and obtain high-quality evidence.

### Study design

2.2

This is a multicenter, open-label, randomized controlled trial. A total of 115 participants will be enrolled, including 100 PSD patients to be randomly allocated in a 1:1 ratio to either the experimental group or the rehabilitation control group, and 15 additional participants will serve as the healthy control group. The study period will include baseline observations and 4 weeks of treatment. The clinical efficacy of acupuncture intervention will be assessed using functional assessment scales on day 15, day 30 during treatment, and at 30 and 60-day follow-ups after treatment completion.

This clinical trial adheres to the Consolidated Standards of Reporting Trials (CONSORT) guidelines (12) and complies with the Standards for Reporting Interventions in Clinical Trials of Acupuncture (STRICTA) (13) to ensure methodological rigor in acupuncture-specific interventions. The study design flowchart is presented in Figure 1.

**FIGURE 1 F1:**
[figure not shown]
Trail flowchart.

### Inclusion criteria

2.3

Patients are eligible for study inclusion if they meet all of the following:

(1)   Fulfill the diagnostic criteria for acute ischemic stroke as defined by the Chinese Guidelines for the Diagnosis and Treatment of Acute Ischemic Stroke (2023 Edition) (14), and have dysphagia confirmed by the Scottish Intercollegiate Guidelines Network (SIGN) recommendations (15).(2)   Age between 18 and 80 years.(3)   FOIS levels between 2 and 4.(4)   Stroke duration of 15–180 days.(5)   Infarction location in the cerebral cortex and subcortical regions.(6)   Patients or their legal guardians must fully understand the study procedures, provide written informed consent, and agree to participate.

### Exclusion criteria

2.4

Patients will be excluded if they have any one of the following:

(1)   Pre-existing dysphagia unrelated to the current stroke.(2)   Life-threatening comorbidities with < 3-month life expectancy.(3)   Severe psychiatric/cognitive impairments affecting study compliance.(4)   Unable to tolerate acupuncture.(5)   Inability to complete standardized swallowing assessments.(6)   Current pregnancy or lactation.(7)   Participated in other clinical trials within 1 month.

### Dropout criteria

2.5

(1)   Subjects who have poor compliance during the clinical trial, or are unwilling to continue participating in the study and withdraw voluntarily.(2)   Those who experience serious adverse reactions, serious complications, or deterioration during the study are unfit to continue.(3)   Subjects who did not follow the treatment protocol or had incomplete observation data that affected the assessment.

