### Sample size, randomization, and blinding

2.7

The primary efficacy outcome is the FOIS score. As neither our team nor previous studies have used this measure to assess acupuncture efficacy for post-stroke dysphagia, it is not possible to determine an appropriate effect size from existing data. A review of similar studies has revealed that after 4 weeks, the FOIS score difference from baseline was 1.31 (rehabilitation training group) vs. 0.31 (sham training group), with a standard deviation of 1.09 (16). This value will be used as the expected effect size for this trial, and sample size calculations will be conducted based on a superiority trial design (17). These parameters (μA = 1.31, μB = 0.31, σ = 1.09, α = 0.05, power = 0.8, δ = 0.39) were applied in a superiority design with 1:1 allocation. After calculation, nA = nB = 40. Considering a 20% dropout rate, this study is expected to enroll 100 patients.

Randomization will use computer-generated numbers to allocate patients equally to acupuncture or rehabilitation groups. A stratified block randomization design will be employed. An independent statistician will generate all random sequences in SPSS 25.0, with study center and baseline FOIS as stratification factors, block lengths of 4 and 6 randomly interleaved, and the seed number set to 20240420. Allocation concealment will be implemented through sequentially numbered, opaque, sealed envelopes kept by a research coordinator who has no conflicts of interest with the study team. After participants have completed baseline assessments and provided written informed consent, the responsible physician will open the corresponding envelope on-site to reveal the allocation. The statistician generating the random sequence will operate independently of the coordinator handling allocation concealment. Neither patients nor physicians will know the allocation in advance. All participants will be followed for 90 days.

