##### Attribution criteria for adverse events

2.9.3.2

To differentiate between adverse events (AEs) causally related to acupuncture intervention and those potentially attributable to pre-existing post-stroke depression (PSD), attribution will be determined in accordance with the CIOMS guidelines (45) and the Standards for Reporting Adverse Events in Acupuncture Clinical Trials (46). Detailed criteria are provided in Table 3.

**TABLE 3 T3:** Severity grading criteria for adverse events.

Severity grade	Core definition	Diagnostic criteria
Mild	Symptoms are mild and do not affect daily life or trial participation	1. Local symptoms: Such as mild soreness at the acupuncture site, transient throat numbness and distension (duration < 30 min); 2. Functional impact: No restrictions on daily activities; able to complete interventions normally; 3. Management requirements: No special treatment needed; symptoms resolve spontaneously.
Moderate	Symptoms are noticeable and may moderately interfere with daily activities or trial procedures; they are amenable to symptomatic treatment.	1. Local symptoms: Such as persistent throat discomfort for 1–2 h after acupuncture, or local skin erythema with a diameter of 2–3 cm; 2. Functional impact: Need to adjust daily activities (e.g., reduce intake of hard foods) but without affecting intervention implementation; 3. Management requirements: Symptomatic treatment required (e.g., lozenges for soothing the throat) and symptoms are alleviable.
Severe	Symptoms are severe and significantly affect daily life or result in inability to continue the trial	1. Local symptoms: Such as severe laryngospasm (duration > 10 min) after acupuncture, or skin redness and swelling with a diameter > 3 cm accompanied by pain; 2. Functional impact: Inability to perform daily activities such as eating and swallowing, or require temporary discontinuation of acupuncture or rehabilitation sessions; 3. Management requirements: Medical intervention required (e.g., oxygen therapy, medication); symptoms alleviate slowly.

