### Evaluation schedule

2.10

FOIS, NIHSS, SWAL-QOL, PAS, and YPR-SRS will be assessed at baseline (pre-treatment), 15 and 30 days after treatment initiation, and 30 and 60 days post-treatment completion. Additionally, fMRI-derived ReHo and ALFF metrics, sEMG evaluations, and PRO scores will be obtained at baseline and at 15 and 30 days following treatment initiation. The study timeline for enrollment, intervention, and assessment is detailed in Table 4. All dropouts and their respective reasons will be systematically documented in the case report forms (CRFs).

**TABLE 4 T4:** Study assessment schedule.

Times outcomes	Before treatment	Treatment				Follow-up	
	Day 3–0	Week 1–2	(Day 15)	Week 2–4	(Day 30)	Day 60	Day 90

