#### Analysis adjusting for treatment expectations

2.12.3

For the primary efficacy outcome (FOIS) and key secondary subjective measures (SWAL-QOL, PRO), analysis of covariance (ANCOVA) or mixed-effects models will be employed, with the total baseline treatment expectation score included as a covariate to control for its potential influence on treatment outcomes.

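### Section 2.5 lists deterioration, serious events, poor compliance and departure from treatment as dropout criteria without saying that only the sessions end and FOIS assessment continues

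*Protocol article*

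**What the plan says.** Section 2.5 is one list headed Dropout criteria.

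- Item (1) covers poor compliance and voluntary withdrawal from the study.
- Item (2) reads: "Those who experience serious adverse reactions, serious complications, or deterioration during the study are unfit to continue".
- Item (3) covers patients who did not follow the treatment protocol or whose observation data were incomplete.

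Other places that bear on it:

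- Section 2.7, follow-up: "All participants will be followed for 90 days".
- Section 2.7, sample size: "Considering a 20% dropout rate, this study is expected to enroll 100 patients".
- Abstract, Methods: "All primary analyses will be conducted using both intention-to-treat and per-protocol approaches".
- Section 2.10 and Table 4 schedule FOIS at baseline and days 15, 30, 60 and 90. For dropouts, 2.10 asks only that they and their reasons be recorded.
- Table 3, severe grade: "Symptoms are severe and significantly affect daily life or result in inability to continue the trial". The same row also mentions patients who "require temporary discontinuation of acupuncture or rehabilitation sessions".
- Section 2.9.3.3 rechecks a patient three days after a serious event is managed, with later treatment in view. It keeps patients with newly abnormal values under examination to the end of follow-up, but it also allows observation to be stopped when laboratory values are abnormal.
- Section 2.12.3, for FOIS and the key subjective measures: "analysis of covariance (ANCOVA) or mixed-effects models will be employed". Section 2.12.5 gives a similar choice between repeated-measures mixed models and multiple linear regression.

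**The concern.** Stopping treatment and stopping observation are different events, and an intention-to-treat analysis depends on keeping them apart. Section 2.5 uses one label for both. Item (1) speaks of taking part in the study, so the phrase about continuing in item (2) is most naturally read as leaving the trial.

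If a site reads it that way, FOIS is lost because of what happened to the patient. Deterioration may itself be a fall in swallowing function. Aspiration pneumonia, which the Introduction names as a consequence of dysphagia and 2.9.3.1 as a possible treatment-related event, is one route into item (2). Poor compliance and departure from treatment, in items (1) and (3), may also be related to how the patient is doing.

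The loss could differ between arms. The trial is open-label, Table 3's local-symptom examples for each grade mainly concern needling, and 2.9.3.3 specifies its immediate adverse-event form for use after acupuncture sessions.

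Analysis cannot fully repair this. A mixed model can use values recorded before the event (baseline and perhaps day 15), but neither it nor the ANCOVA or regression alternative sees a fall that comes after the last recorded value.

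**Working it through.** **1. The plan's own figures.** Section 2.7 gives changes of 1.31 and 0.31, SD 1.09, alpha 0.05, power 0.8 and margin 0.39.

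n per arm = 2 × SD² × (z_alpha + z_power)² / (difference − margin)²
= 2 × 1.09² × (1.645 + 0.842)² / (1.00 − 0.39)²
≈ 14.7 / 0.372 ≈ 39.5, rounded up to 40.

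This uses a one-sided alpha of 0.05; two-sided gives 51. Inflation: 40 / 0.8 = 50 per arm, 100 in total. The stated figures reproduce, so the sample size is not the issue. The step shows only that up to 10 per arm are budgeted under the word dropout.

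**2. What the texts say when set side by side.**

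| Place | Points to |
|---|---|
| 2.5, heading and item (1) beside item (2) | Leaving the trial |
| 2.7, 90-day follow-up of everyone | Assessment continues |
| Abstract, intention-to-treat | All randomised patients analysed |
| 2.10 and Table 4 | FOIS to day 90, no exception stated; dropouts only recorded |
| Table 3, severe grade | Both, within one row |
| 2.9.3.3 | Mostly continued follow-up, with discretion to stop observation |

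No row says that FOIS stops under 2.5, and none says that it continues.

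**3. What could be at stake.** Let dA and dB be the patients left out at day 30 in the acupuncture (A) and control (B) arms of 50. Let mA and mB be the mean FOIS changes in those still assessed, and c the mean change in those left out. The shift is the difference among those assessed minus the difference among all randomised:

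shift = (dA/50)(mA − c) − (dB/50)(mB − c)

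Only 1.31, 0.31 and 0.39 come from 2.7. The counts, c and the equal-gain scenario are assumptions.

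| mA, mB | c | dA, dB | Shift |
|---|---|---|---|
| 1.31, 0.31 | −1 | 1, 1 | 0.046 − 0.026 = +0.02 |
| 1.31, 0.31 | −1 | 5, 5 | 0.231 − 0.131 = +0.10 |
| 1.31, 0.31 | −1 | 5, 1 | 0.231 − 0.026 = +0.205 |
| 1.31, 0.31 | −1 | 1, 5 | 0.046 − 0.131 = −0.085 |
| 1.31, 0.31 | 0 | 5, 1 | 0.131 − 0.006 = +0.125 |
| 1.31, 0.31 | 0 | 1, 5 | 0.026 − 0.031 = −0.005 |
| 1.31, 1.31 | −1 | equal | 0 |
| 1.31, 1.31 | −1 | 5, 1 or 1, 5 | ±(0.231 − 0.046) = ±0.185 |

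**4. If the three items together used the dropout allowance.** With a difference of 1.00 among those assessed, the all-randomised difference would be:

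- 20% left out in both arms: 0.80, whatever c is.
- 20% in A, 10% in B: 0.67 (c = −1) to 0.77 (c = 0).
- 20% in A, none in B: 0.54 to 0.74.
- 10% in A, 20% in B: 1.03 (c = −1) to 0.93 (c = 0).

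The shift can go either way and depends mainly on imbalance between arms. These are complete-case figures. A mixed model using earlier values could give smaller shifts.

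**The case against.** The strongest defence is that the explicit text favours continued follow-up. Section 2.7 promises 90 days for everyone, the Abstract commits to intention-to-treat, Table 4 makes no exception, and most of 2.9.3.3 keeps patients under observation. Item (2) can be read as unfit for further treatment, and then nothing conflicts. The article also condenses a fuller protocol, and Figure 4, on adverse-event management, is not shown and may settle the matter.

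Much of this stands. A reader might infer that 2.5 removes these patients from FOIS assessment or from the intention-to-treat set, or that it flatly contradicts 2.7. The documents do not support that, since no sentence says either thing. Table 3 is weak support because it grades severity and is not a withdrawal rule. The 20% allowance is ordinary inflation and does not say that dropouts go unassessed.

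A reader might also infer a bias in favour of acupuncture. That is not supported either: the counts are assumed, the direction depends on them, and even the +0.20 case at the planned effect leaves an all-randomised difference of about 0.80, roughly twice the margin.

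What the defence does not remove is that 2.5 is a printed rule that governs conduct at the sites. Its natural reading differs from the follow-up promise, and FOIS values never collected cannot be supplied by a later analysis plan.

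**Conclusion.** The point holds as a badly fixed rule, in tension with 2.7 and the Abstract. It is not a demonstrated contradiction or a demonstrated bias. It applies to all of 2.5: item (2) is the clearest case because it is tied to outcome, but items (1) and (3) leave the same gap.

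Size and direction are unknown. Under the assumption of 1 to 5 patients per arm left out, the shift runs from −0.08 to +0.20 with c = −1 and from 0.00 to +0.12 with c = 0. If both arms gain 1.31, it is zero for equal numbers and ±0.18 for 5 versus 1. A change of −1 is pessimistic, since deterioration need not concern swallowing. The change should be made because it is cheap and the possible loss cannot be undone. Confidence is medium, given the missing figure and the unseen full protocol.

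**What to change.** Reword section 2.5 as a whole. Changing item (2) alone is not enough, because a patient taken off sessions could still be classed as a dropout under item (3). Suggested content:

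- Poor compliance (item 1), a serious reaction, serious complication or deterioration judged to make the patient unfit (item 2), and departure from the treatment protocol (item 3) end the assigned sessions only, or affect membership of the per-protocol set only.
- FOIS and adverse-event follow-up continue at the scheduled visits to day 90 unless the patient withdraws consent.
- All randomised patients stay in the intention-to-treat set.
- FEES-based PAS and YPR-SRS continue only when clinically safe.

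Section 2.6 gives recruitment as April 2024 to June 2025. Ninety days after June 2025 is about September 2025, before the article appeared in December 2025. If follow-up has ended, rewording recovers nothing. The report should then state how 2.5 was applied in each arm, how many patients it affected, and whether FOIS was collected after the event.

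The cost is a few reworded lines and some effort to follow patients who are off treatment. No visits are added, since days 15, 30, 60 and 90 are already in Table 4.

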### Recruitment of study participants

2.6

The study will be conducted at two hospitals of Hunan University of Traditional Chinese Medicine (First and Second Affiliated Hospitals), with the Second Affiliated Hospital leading study design and implementation. PSD participants will be recruited from hospital wards/clinics (April 2024-June 2025), while healthy controls will be enrolled from the community during the same period.

### Sample size, randomization, and blinding

2.7

The primary efficacy outcome is the FOIS score. As neither our team nor previous studies have used this measure to assess acupuncture efficacy for post-stroke dysphagia, it is not possible to determine an appropriate effect size from existing data. A review of similar studies has revealed that after 4 weeks, the FOIS score difference from baseline was 1.31 (rehabilitation training group) vs. 0.31 (sham training group), with a standard deviation of 1.09 (16). This value will be used as the expected effect size for this trial, and sample size calculations will be conducted based on a superiority trial design (17). These parameters (μA = 1.31, μB = 0.31, σ = 1.09, α = 0.05, power = 0.8, δ = 0.39) were applied in a superiority design with 1:1 allocation. After calculation, nA = nB = 40. Considering a 20% dropout rate, this study is expected to enroll 100 patients.

Randomization will use computer-generated numbers to allocate patients equally to acupuncture or rehabilitation groups. A stratified block randomization design will be employed. An independent statistician will generate all random sequences in SPSS 25.0, with study center and baseline FOIS as stratification factors, block lengths of 4 and 6 randomly interleaved, and the seed number set to 20240420. Allocation concealment will be implemented through sequentially numbered, opaque, sealed envelopes kept by a research coordinator who has no conflicts of interest with the study team. After participants have completed baseline assessments and provided written informed consent, the responsible physician will open the corresponding envelope on-site to reveal the allocation. The statistician generating the random sequence will operate independently of the coordinator handling allocation concealment. Neither patients nor physicians will know the allocation in advance. All participants will be followed for 90 days.

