#### Primary outcomes

2.9.1

The Functional Oral Intake Scale (FOIS) is a validated 7-point ordinal scale that assesses functional feeding status, ranging from tube feeding dependence (level 1) to unrestricted oral intake (level 7) (24). It will be used to assess the functional oral intake of PSD patients and as a eligibility criterion for selecting participants. Existing evidence indicates that acupuncture typically improves FOIS scores by 1–2 points (25), though treatment response varies with baseline characteristics, specific acupuncture parameters and intervention duration. For patients with initial scores of 2–4, achieving normal swallowing levels (FOIS ≥ 6) after 4 weeks of acupuncture treatment will be considered indicative of treatment effectiveness (26). The FOIS has been well-established as a reliable outcome measure for tracking longitudinal changes in swallowing function among stroke patients (27). Its standardized design and clinical relevance have led to widespread adoption in dysphagia research.

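### The sample size borrows a rehabilitation-versus-sham difference, but the control arm here receives rehabilitation, so the 80% power is not supported for the comparison this trial makes

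*Protocol article*

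**What the plan says.** Section 2.7 explains that no suitable effect size exists for acupuncture: "As neither our team nor previous studies have used this measure to assess acupuncture efficacy for post-stroke dysphagia". It therefore turns to a similar study in which, after 4 weeks, "the FOIS score difference from baseline was 1.31 (rehabilitation training group) vs. 0.31 (sham training group), with a standard deviation of 1.09". It then says: "This value will be used as the expected effect size for this trial". The parameters are "μA = 1.31, μB = 0.31, σ = 1.09, α = 0.05, power = 0.8, δ = 0.39", and they "were applied in a superiority design with 1:1 allocation". The result is 40 per arm, raised to 100 enrolled for 20% dropout. Whether α is one-sided or two-sided is not stated.

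The Abstract (Methods) describes the comparator as "the control group (rehabilitation training combined with basic treatment"), and sections 2.2 and 2.8.2 agree. The Discussion calls swallowing rehabilitation the gold standard. Section 2.9.1 says of the primary outcome that "acupuncture typically improves FOIS scores by 1–2 points".

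**The concern.** The borrowed study reports a mean for the treatment that this trial uses as its control: rehabilitation, 1.31. The plan assigns that mean to the acupuncture arm and assigns the sham mean, 0.31, to the rehabilitation arm. The assumed 1.0-point difference is thus the effect of rehabilitation over sham. It says nothing about acupuncture against rehabilitation.

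This is the only power statement for the primary outcome. If it stands, a non-significant result may be read as showing that acupuncture is as good as rehabilitation, on the belief that the trial had 80% power to find a difference. The reason given for borrowing also conflicts with section 2.9.1: one section says no study has used FOIS for acupuncture in this condition, and the other quotes FOIS gains with acupuncture.

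**Working it through.** **Inputs.** From section 2.7: means 1.31 and 0.31, SD 1.09, α = 0.05, power 0.80, δ = 0.39, 20% dropout. From section 2.9.1: acupuncture gain of 1–2 points.

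**Step 1: reproduce the plan's figure.** Treat δ as a superiority margin and test one-sided:

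n per arm = 2 × (1.645 + 0.842)² × 1.09² / (1.00 − 0.39)² = 39.5, so 40.

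80 / (1 − 0.20) = 100 enrolled.

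This matches. The alternatives do not:
- two-sided with the margin: 51 per arm
- no margin: 15 (one-sided) or 19 (two-sided)
- 0.39 taken as the difference itself: 97 or 123

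One-sided 5% with a 0.39 margin is therefore inferred from the arithmetic. The article does not state it.

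**Step 2: set the control mean to the source's rehabilitation figure.** Assumptions: the control gains 1.31; the 1–2 points are changes from baseline; SD 1.09 holds. The expected difference runs from 1.0 − 1.31 = −0.31 to 2.0 − 1.31 = +0.69.

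**Step 3: power at 40 per arm.** SE = 1.09 × √(2/40) = 0.2437. Power is from the noncentral t distribution with 78 degrees of freedom and noncentrality (difference − margin) / SE.

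| Acupuncture gain | Difference | Margin 0.39, one-sided 5% | No margin, two-sided 5% |
|---|---|---|---|
| 1.5 | 0.19 | 0.7% | 12% |
| 1.75 | 0.44 | 7.5% | 43% |
| 2.0 | 0.69 | 34% | 80% |
| 2.31 | 1.00 | 80% | 98% |

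Below a gain of 1.31 the difference is negative and power to show superiority is close to zero under either test.

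**Step 4: detectable difference at 80% power, 40 per arm.**
- With the margin, one-sided 5%: 0.39 + (1.645 + 0.842) × 0.2437 = 0.996, or about 1.0 point. The control being at 1.31, acupuncture must gain about 2.31, above the 1–2 range.
- No margin, two-sided 5%: (1.960 + 0.842) × 0.2437 = 0.683 by the normal approximation and 0.691 by noncentral t, so about 0.69 points. Acupuncture must gain about 2.0, the top of the range.

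**Step 5: what the plan's own formula would need at a gain of 2.0.** 2 × (1.645 + 0.842)² × 1.09² / (0.69 − 0.39)² = 163.2, so 164 per arm, or 410 enrolled after 20% dropout.

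**The case against.** *Borrowing is normal when data are lacking, and the article admits that they are.* Borrowing a magnitude can be defended. Here, however, the source names this trial's control treatment and gives its mean, and the plan uses that mean for the other arm. The limitations paragraph concedes that a small sample may reduce power, but does not say that the 80% refers to a different comparison.

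*Section 2.8 could mean rehabilitation for everyone, with acupuncture added.* It does place swallowing rehabilitation in the paragraph on treatment for all participants, and on that reading active-versus-sham would be a less unreasonable proxy for the added effect. The Abstract, Introduction and Discussion favour a head-to-head comparison. On either reading the control arm receives rehabilitation, so 0.31 is not its figure.

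*The 1–2 points may be an advantage over a control.* Section 2.9.1 names no comparator and gives no SD, and the calculation does not use the figure. Change from baseline is the more natural reading, but it remains an assumption. If the figure were a between-group advantage, 1.0 would sit at its low end. Likewise, nothing shows that the training and patients in the borrowed study match section 2.8.2, so 1.31 for this control arm is also an assumption. Both objections stand as limits on the size of the problem.

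*The lowest power figures rest on a margin that the analysis sections do not mention.* This is correct: sections 2.12.2 to 2.12.5 describe covariance analysis, mixed models and regression without a 0.39 margin. A reader might infer from the table that a null result is likely wherever acupuncture falls in the 1–2 range. The article does not support that: at a gain of 2.0 and with no margin tested, power is about 80%. A reader might also take the one-sided test as the stated design, but it is only the variant that gives 40.

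*The two sections on FOIS evidence may not conflict.* Section 2.7 is limited to post-stroke dysphagia, while the sentence in 2.9.1 names no population. This is a secondary wording point, but the sections need reconciling because the first is the stated reason for borrowing.

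**Conclusion.** The concern holds. The arithmetic is sound: 40 per arm and 100 enrolled follow from the stated inputs. The inputs describe rehabilitation against sham, and no part of the article supports a 1.0-point advantage of acupuncture over rehabilitation. The 80% power is therefore not supported for this trial's contrast.

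The size is conditional on the three assumptions in Step 2. Under them, power is at most about 34% across the 1–2 point range if the 0.39 margin is tested one-sided. If no margin is tested (two-sided 5%), it reaches about 80% at a gain of 2.0 and falls to 43% at 1.75 and 12% at 1.5. Only the top of the range is adequately powered, and only without the margin.

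This does not show that the trial must fail, nor that acupuncture is no better than rehabilitation. It shows that the power claim cannot be used to interpret the result.

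**What to change.** Keep 100 patients and rewrite the planning paragraph in section 2.7:

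1. Say that the borrowed figures are rehabilitation versus sham, and withdraw the claim of 80% power for an expected 1.0-point advantage of acupuncture over rehabilitation.
2. State whether the primary test is one-sided or two-sided, and whether the 0.39 margin applies to it. Dropping the margin is a change of design and should be declared as one.
3. Give the matching detectable difference for 40 evaluable per arm at 80% power and SD 1.09: about 1.0 point with the margin (one-sided 5%), or about 0.69 points without it (two-sided 5%).
4. State that a non-significant result will be read through the confidence interval for the difference and not as equivalence to rehabilitation.
5. Reconcile the statement in 2.7 that FOIS has not been used for acupuncture with the 1–2 point evidence in 2.9.1, and say whether those points are change from baseline or advantage over a control.

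The cost is rewording and a less favourable power statement. No patients, visits or data are added. The change makes the weakness visible but does not raise the power.
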